#### Secondary outcomes

The secondary outcomes are the effect on ECG [25], change in Seattle Angina Questionnaire (SAQ) scores [26], and nitroglycerine consumption during the treatment period. Patients will be asked to complete an SAQ (at the baseline period and at the end of the 4-week treatment), which is a 19-item self-administered questionnaire, to measure five dimensions of health. Researchers will record nitroglycerine consumption during the treatment period and compare this among groups.

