### Sample size {14}

The sample size is calculated using PASS 15 software (NCSS, Kaysville, UT) and driven by the efficacy rate of stable angina symptom score improvement. According to the referenced literature [27, 28], the efficacy rate in relieving stable angina symptoms of NXT is expected to be 85%, 70% for BYHW, and 50% for placebo.

The PASS parameters are as follows: “Proportions>Contingency Table (Chi-Square Tests)>Chi-Square Tests”, “Chi-Square Effect Size Estimator> Contingency Table”. Input the percentage values: placebo = 50%, BYHW = 70%, NXT = “85%”, copy effect size = “0.308210”. Design solve for “sample size”, DF = 2, Power = 0.8, Alpha = 0.05, input effect size = “0.308210”. Then we can get numeric results: *N* = 102, Chi-square = 9.6893, Alpha = 0.05000, Beta = 0.19763. Considering a drop rate of 20%, the dropout-inflated sample size = 128, and expected number of dropouts = 26. According to the ratio of 2:1:1, there will be 64 cases in intervention group 1, 32 cases each in the intervention group 2 and control group. Since this study intends to further compare the NXT and BYHW groups, according to NXT = 85%, BYHW = 70%, W = 0.3082, DF = 1, and the sample size of NXT and BYHW calculated in the previous step, we can reach a power of 0.85540.

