## Assignment of interventions: allocation

### Sequence generation {16a}

Eligible participants will be randomized in a 2:1:1 ratio into intervention group 1, intervention group 2, or the control group based on a computer-generated (SAS 9.4 statistical software package PROC PLAN process) random sequence. The randomization sequence will be recorded by staff at the sponsor unit, and the randomized code of the trial drug is the unique identification code of participants. Eligible participants will be randomized in blocks of eight within each site and stratified by site.

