## Statistical methods

### Statistical methods for primary and secondary outcomes {20a}

The statistical analysis plan will be specified before data analysis. Statistical Analysis System v9.4 (or a higher version) will be used for statistical analysis. Professional statisticians who are independent of all other processes in our study will carry out the analyses.

For continuous variables, we will calculate the mean, standard deviation, median, minimum, maximum, and interquartile range. For categorical variables, we will report various frequencies or percentages. The chi-square test or Fisher’s exact test will be used for categorical variables. For variables with a normal distribution, intergroup comparisons will be analysed with one-way ANOVA, whereas pairwise comparisons before and after treatment will be performed with Student’s *t* test. For data that do not have a normal distribution, intragroup or intergroup differences before and after treatment will be analysed by the Wilcoxon rank-sum test. The proportion of patients with AEs will be compared using the chi-square test or Fisher’s exact test.

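### The Wilcoxon rank-sum test is named for paired before-after data within an arm, where it is the wrong test, and it cannot stand in for one-way ANOVA across three arms

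*Protocol article*

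**What the plan says.** The section on statistical methods for primary and secondary outcomes (item 20a) sets out two branches for continuous data.

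- **Normal data:** "intergroup comparisons will be analysed with one-way ANOVA", and "pairwise comparisons before and after treatment will be performed with Student"'s *t* test.
- **Non-normal data:** a single test for both purposes: "intragroup or intergroup differences before and after treatment will be analysed by the Wilcoxon rank-sum test".

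The article names neither the Wilcoxon signed-rank test nor the Kruskal-Wallis test.

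The design around this rule is as follows.

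- **Three arms (items 16a and 14):** "Eligible participants will be randomized in a 2:1:1 ratio into intervention group 1, intervention group 2, or the control group", and "there will be 64 cases in intervention group 1, 32 cases each in the intervention group 2 and control group".
- **Repeated measurement (Secondary outcomes):** the SAQ is completed "at the baseline period and at the end of the 4-week treatment". Table 4 likewise schedules the efficacy indicators at both baseline and the intervention period.
- **Nitroglycerine (Secondary outcomes):** "Researchers will record nitroglycerine consumption during the treatment period and compare this among groups". Table 3 lists it as a count summarised by the median.
- **Contrasts (item 6b):** each active arm against placebo, and NXT against BYHW.

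**The concern.** A before-after comparison inside one arm sets each patient's day-28 value against the same patient's baseline value. The rank-sum test treats those two sets as if they came from different people. It therefore uses a variance that ignores the within-patient correlation, and its p-value is wrong.

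There is a second, smaller fault in the same sentence. The rank-sum test compares two samples. The normal branch gives an overall test over all three arms, while the non-normal branch names only a two-sample test, although nitroglycerine consumption is to be compared among three groups.

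At stake are the p-values for secondary outcomes and continuous safety measures that turn out non-normal. Nitroglycerine consumption is the likeliest case. SAQ scores, vital signs and laboratory values may follow, since Table 3 allows mean or median for each.

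**Working it through.** **1. Is there a figure in the plan to reproduce?** None is attached to the rank-sum rule. The sample size (item 14) rests on a chi-square test of the primary proportion: noncentrality = N × w² = 102 × 0.308210² = 9.6893, beta = 0.19763, and 102 / (1 − 0.20) = 127.5, rounded up to 128. These match the stated values and involve no rank test, so the sample size does not depend on this point.

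**2. Within an arm: type I error by a variance argument.** The rank-sum statistic is in effect a difference of two mean ranks. For two independent samples of size n its variance is proportional to 2σ²/n. For paired samples with rank correlation ρₛ it is 2σ²(1 − ρₛ)/n. The test uses the first when the second is true, so the nominal 5% test rejects with probability

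2 × [1 − Φ(1.96 / √(1 − ρₛ))], where for normal scores ρₛ = (6/π) × arcsin(ρ/2).

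The documents give no before-after correlation ρ, so 0.3 to 0.7 is an assumption.

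| Assumed ρ | ρₛ | 1.96/√(1 − ρₛ) | True type I error |
|---|---|---|---|
| 0.3 | 0.288 | 2.32 | 2.0% |
| 0.5 | 0.483 | 2.73 | 0.6% |
| 0.7 | 0.683 | 3.48 | 0.05% |

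**3. Within an arm: the same by simulation.** With 20,000 runs per case, bivariate normal scores and n = 64, the rank-sum test rejected in 1.95%, 0.65% and 0.03% under no change; the signed-rank test rejected in 4.8%, 4.9% and 4.9%. A run with log-normal data (6,000 per case, n = 32 and 64) gave 2.1–2.3%, 0.7% and 0.05–0.1% for rank-sum, and 4.6–5.2% for signed-rank. This second run is not independent evidence about distributional shape: the rank-sum test is unchanged by taking logs, and the signed-rank test was applied to log differences.

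**4. Within an arm: power.** Assumed shift 0.4 SD (log scale for counts), n = 32, correlations 0.3 / 0.5 / 0.7:

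| Data | Rank-sum | Signed-rank | Loss (points) |
|---|---|---|---|
| Normal scores | 31 / 28 / 25% | 44 / 57 / 79% | 13 / 29 / 54 |
| Skewed counts with zeros and ties | 24 / 22 / 18% | 31 / 35 / 53% | 7 / 13 / 35 |

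The counts (log-normal values rounded down, 2,000 runs) resemble nitroglycerine consumption more closely. Their null rejection rate with rank-sum was 1.8%, 1.4% and 0.4%. The fault remains, but the power loss is smaller.

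**5. Between groups.** With arms of 64, 32 and 32 and no true difference (20,000 runs), each single two-arm rank-sum test rejected in 4.8–5.2%, so the test is valid for the contrasts of item 6b. Kruskal-Wallis, the rank counterpart of one-way ANOVA, rejected in 5.0%. The rank-sum test itself yields no single p-value over three arms.

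**The case against.** Several points can fairly be made for the plan.

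- **The analysis plan will settle it.** Item 20a says that the plan will be specified before data analysis, and the lack of an overall rank test, taken alone, could be left to it. That does not excuse the within-arm half: the protocol states a wrong test, and an analysis plan that followed it would repeat the error.
- **It may be a slip for signed-rank.** Then the sentence would be right within arms and wrong between groups. No one test serves both uses, so the sentence needs correcting on either reading.
- **Within-arm tests decide no objective.** This stands. The objectives and every efficacy metric in Table 3 concern differences between groups, which limits the consequence.

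A reader might also infer more than the documents support.

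- **That rank-sum is wrong for all between-group use.** It is not. The text says intergroup, and item 6b plans two-arm contrasts for which the test is valid. The three-arm reading rests on the parallel with ANOVA and on the among-groups comparison of nitroglycerine.
- **That the *t* test is meant to be unpaired.** The words "pairwise comparisons before and after treatment will be performed with Student" can naturally be read as paired.
- **That false-positive findings or a faulty primary analysis result.** With positive correlation the within-arm error makes rejection rarer. The primary outcome is a proportion, tested by chi-square or Fisher's exact test.

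**Conclusion.** The point holds in a limited form. Assigning the rank-sum test to before-after differences within an arm is a misstatement. With positive correlation, which is to be expected when the same patient is measured twice, the test is conservative and loses power. The type I error figures of about 2%, 0.7% and below 0.1% rest on normal scores and assumed correlations of 0.3, 0.5 and 0.7. The power losses rest in addition on an assumed 0.4 SD shift, and those from normal scores should not be carried over to nitroglycerine counts, where they are smaller.

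Between groups, the fault is only that a two-sample test is named where the same paragraph uses a three-arm test for normal data.

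The reach is limited to non-normal secondary and continuous safety measures. The plan should be corrected, but no primary conclusion hangs on it.

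**What to change.** Replace the non-normal sentence in item 20a, and carry the change into the statistical analysis plan, with a rule to this effect:

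- change within an arm: Wilcoxon signed-rank test;
- overall comparison of the three arms: Kruskal-Wallis test;
- NXT against placebo, BYHW against placebo, and NXT against BYHW: Wilcoxon rank-sum test.

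The cost is one sentence. No extra data or patients are needed, and the Trial status section reports that no analysis has yet been carried out, so the change can be made before any analysis.

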### Interim analyses {21b}

Since the number of recruited cases is not large, no interim analysis is planned.

### Methods for additional analyses (e.g. subgroup analyses) {20b}

We will include sex, centre, complications, and concomitant medication as covariates in an analysis of covariance (ANOVA) for significant differences between groups by reducing the error variance.

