***Secondary outcomes***				
ECG parameters	Classification of 12-lead ECG improvement [23]	Difference between two groups	Proportion	Baseline, 28 days after treatment
SAQ scores	SAQ [24]	Difference in the change between groups	Mean/ median	Baseline, 28 days after treatment
Nitroglycerin consumption	Count	Compare the difference between groups	Median	Baseline, 28 days after treatment

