**Other works**			
Drug distribution	×	×	
Drug recycling		×	×
Record adverse events and combined medication		×	×
Compliance judgement		×	×

*ALT* alanine aminotransferase, *AST* aspartate aminotransferase, *AP* alkaline phosphatase, *TBIL* total bilirubin, *γ-GT* γ-glutamyl transpeptidase, *SCr* serumcreatinine, *BUN* blood urea nitrogen, *PT* prothrombin time, *APTT* activated partial thrombolastin time, *TT* thrombin time, *FIB* fibrinogen, *INR* international normalized ratio

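### The SAQ is compared as unadjusted change, and the one covariate model meant to reduce error variance leaves out the baseline score and does not fix when two of its covariates are recorded

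*Protocol article*

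**What the plan says.** **Outcome.** Secondary outcomes sets two SAQ assessments: "Patients will be asked to complete an SAQ (at the baseline period and at the end of the 4-week treatment". The questionnaire yields five dimensions. Table 3 gives the SAQ metric as "Difference in the change between groups", summarised by mean or median.

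**Main tests.** Statistical methods {20a} gives a general rule for continuous variables: "For variables with a normal distribution, intergroup comparisons will be analysed with one-way ANOVA". Otherwise, "intragroup or intergroup differences before and after treatment will be analysed by the Wilcoxon rank-sum test". Neither route carries a covariate.

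**Covariate model.** Methods for additional analyses {20b} states: "We will include sex, centre, complications, and concomitant medication as covariates in an analysis of covariance (ANOVA". The sentence gives error-variance reduction as the aim. It names no outcome, does not list a baseline score, and expands the abbreviation ANOVA as analysis of covariance.

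**Timing of two of the covariates.** Table 4 marks the rows for concomitant medication and for complications and symptoms in the run-in column only. A separate row, "Record adverse events and combined medication", is marked at baseline and in the intervention period.

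**The concern.** A model whose purpose is to reduce error variance would normally start with the baseline value of the outcome, usually its strongest predictor. Here that value is collected from every patient and left off the list, while sex, centre and two loosely defined covariates are included. The SAQ comparison is therefore less precise than the data allow.

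A second, smaller matter is that {20b} does not say when complications and concomitant medication are measured. Table 4 points to run-in. But {11d} uses the term concomitant medication for what is recorded during the trial, and {11b} uses complications for events during the trial. The permitted concomitant therapies in {11a} include sublingual nitroglycerine for attacks, and nitroglycerine consumption is itself a secondary outcome. If an analyst took values from after randomisation, the model could adjust for something that treatment had changed.

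**Working it through.** **1. The plan's own figure.** There is none for the SAQ. The only sample size, in {14}, is for the symptom efficacy rate: effect size 0.308210, 2 degrees of freedom, alpha 0.05. The non-centrality is 102 × 0.308210² = 9.6893, which gives power 0.8024, agreeing with the stated beta of 0.19763. Then 102 / (1 − 0.20) = 127.5, rounded up to 128. These figures reproduce, and the SAQ plays no part in them.

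**2. Cost of leaving out baseline.** Assume the same SD, s, at both visits and correlation r between baseline and day 28. The protocol gives neither.
- Variance of change: 2s²(1 − r)
- Residual variance of ANCOVA on baseline: s²(1 − r²) = s²(1 − r)(1 + r)
- Ratio, ANCOVA to change: (1 + r)/2

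For illustration, power is shown for an assumed difference of 0.5 SD in the comparison of 64 with 32 patients (allocation from {14}, no dropout): Φ(0.5/SE − 1.96), where SE = σ√(1/64 + 1/32) = 0.2165σ and σ² is the variance in the table.

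| Assumed r | Change, 2(1−r) | ANCOVA, 1−r² | Ratio | Patients needed, change relative to ANCOVA | Power, change | Power, ANCOVA |
|---|---|---|---|---|---|---|
| 0.3 | 1.40 | 0.91 | 0.65 | 1.54 | 0.497 | 0.678 |
| 0.5 | 1.00 | 0.75 | 0.75 | 1.33 | 0.637 | 0.760 |
| 0.7 | 0.60 | 0.51 | 0.85 | 1.18 | 0.846 | 0.899 |
| 0.8 | 0.40 | 0.36 | 0.90 | 1.11 | 0.955 | 0.971 |

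Worked row, r = 0.5: change has σ = 1, so 0.5/0.2165 = 2.309 and Φ(0.349) = 0.637.

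**3. Where the loss comes from.** The difference between the two variances is 2(1 − r) − (1 − r²) = (1 − r)². A change score subtracts baseline with coefficient 1, whereas the regression slope under these assumptions is r. A chance baseline difference d therefore shifts the change estimate by −(1 − r)d. One standard error of d is 0.22 SD for 64 vs 32 and √(2/32) = 0.25 SD for 32 vs 32. At r = 0.5 these give shifts of about 0.11 and 0.125 SD. Such shifts average to zero over randomisations and are already counted in the variance in step 2; they are not an additional harm.

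**4. Why covariate timing matters.** In an illustrative simulation of 400,000 patients, treatment lowered medication use after randomisation, and a latent severity factor affected both medication use and outcome. With use at 39% in controls and 30% on treatment, adjusting for it turned a true effect of 0.50 SD into about 0.45; at 40% vs 21%, into about 0.40. A true null became about −0.05 and −0.10. When treatment did not affect use, there was no bias. All of these settings are assumptions; the protocol gives no usage rates.

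**The case against.** The strongest reply is that a condensed article may leave model details for a secondary outcome to the statistical analysis plan, which {20a} says will be specified before data analysis. Timing of covariates and a baseline term are typical of what such a plan settles. That stands in part. But this article does more than stay silent: it names the tests and lists the covariates. A plan that follows it inherits the omission, and one that departs from it has to explain why.

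It is also fair to say that change is a valid analysis, that the gain falls to about 11% in patient numbers at r = 0.8, and that the SAQ has no power target. All of that stands, and it limits the point to efficiency.

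Three stronger readings are tempting and are not supported.
- *A reader might infer that the trial will adjust for drugs started after randomisation.* The document does not say so. The wording in {20b} matches the run-in rows of Table 4, and the row for the intervention period uses a different term, combined medication. Background cardiac therapy must also stay at a constant dose, and new symptomatic drugs are allowed only if they do not interfere with assessment of the study drug. The use of the same terms in {11b} and {11d} makes the text ambiguous, no more.
- *A reader might infer that the SAQ estimate will be biased.* Randomisation protects the unadjusted change score; only a covariate affected by treatment could introduce bias.
- *A reader might state as fact that the SAQ is analysed by ANOVA of change.* That joins the general rule in {20a} to Table 3. The Wilcoxon route is equally open, and {20b} names no outcome. Neither main route uses baseline as a covariate, so the point survives either way.

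**Conclusion.** The point holds as a precision issue on a secondary outcome. For assumed correlations of 0.3 to 0.8, adding the baseline score would reduce the variance of the SAQ comparison by 35% down to 10% relative to unadjusted change. This rests on equal variances at both visits and on a least-squares analysis; the formula does not describe the Wilcoxon route exactly, though that route also makes no baseline adjustment. The SAQ is the natural continuous efficacy outcome for the model in {20b}, but that is an inference.

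The timing of complications and concomitant medication is a wording ambiguity to close, not an error that the plan commits. The primary outcome, a proportion tested by chi-square or Fisher's exact test, and the sample size of 128 are not affected. A change is worth making but is not critical.

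**What to change.** - In {20a}, state that each day-28 SAQ dimension will be analysed by ANCOVA with arm, site and that dimension's baseline score. Site belongs in the model because {16a} stratifies randomisation by it.
- In {20b}, name the outcome or outcomes to which the covariate model applies, add the baseline score to the list, and correct the label so that it no longer equates analysis of covariance with ANOVA.
- State that complications and concomitant medication mean the values recorded before randomisation, so that drugs started or events occurring afterwards are not adjusted for.

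The cost is wording only. Table 4 already schedules the SAQ at baseline and both covariates at run-in, so no new data, visits or patients are needed. According to Trial status, no analysis has been carried out, so the change can be made before any data are examined.

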### Methods in analysis to handle protocol non-adherence and any statistical methods to handle missing data {20c}

This study will be consistent with the CONSORT statement and intention-to-treat (ITT) principle, and the last observation carried forward method will be used for missing values. The full analysis set (FAS) is defined as all randomized patients who receive at least one dose of study medication. The per-protocol analysis set is defined as all eligible patients who are at least 80% compliant with the study drug and do not take the prohibited drugs during their time in the study. Analysis of the primary outcome and curative effect will be carried out using full-analysis-set and per-protocol-set approaches. The safety analysis set will include all randomized patients who have accomplished at least one study visit. Participating centres will be required to sum up the participant numbers in each centre and list participants who have been removed from the per-protocol set.

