### Outcomes {12}

#### Primary outcome

The primary outcome is the efficacy rate of stable angina symptom score classification [24]. The stable angina symptom score includes the attack frequency, duration, activity level of effort-induced angina pectoris, and pain degree. The indicators of the baseline period (0 weeks) and treatment period (28 days) will be compared.

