**Efficacy indicators**			
Stable angina symptom score		×	×
Electrocardiogram		×	×
Seattle Angina Questionnaire		×	×
Nitroglycerin consumption	×	×	×

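### With one post-baseline score, LOCF in the full analysis set carries baseline forward, an analysis that the sample size's 80% power does not describe

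*Protocol article*

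**What the plan says.** **Missing data.** Protocol section {20c} states that "the last observation carried forward method will be used for missing values". The FAS there holds every randomized patient who took at least one dose. The primary outcome is analysed in both the FAS and the per-protocol set, and neither is named as primary.

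**Timing of the outcomes.** Under Primary outcome: "The indicators of the baseline period (0 weeks) and treatment period (28 days) will be compared". Table 3 gives the same two time points for the symptom score, ECG and SAQ. In Table 4, the row "Stable angina symptom score" is marked in the baseline column and in the single intervention column (28 ± 4 days); the ECG and SAQ rows are marked in the same way. Section {11c} describes weekly dispensing with a check of drug use and adherence, but no efficacy score is listed for those contacts.

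**After withdrawal.** Section {11b} stops data collection at withdrawal and uses what already exists. Section {11d} separately classes patients who deteriorate and stop as treatment failures.

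**Sample size.** Section {14} is "driven by the efficacy rate of stable angina symptom score improvement" and assumes that "the efficacy rate in relieving stable angina symptoms of NXT is expected to be 85%, 70% for BYHW, and 50% for placebo". It solves for N = 102 and reports "Chi-square = 9.6893, Alpha = 0.05000, Beta = 0.19763". It then adds: "Considering a drop rate of 20%, the dropout-inflated sample size = 128, and expected number of dropouts = 26". The 128 are split 64/32/32.

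**The concern.** LOCF needs an intermediate observation to carry. Here there is none: for a dosed patient who leaves before the day-28 assessment, the last recorded score is the baseline score. LOCF becomes baseline carried forward, and the imputed change is exactly zero. The article does not give the responder cut-off, but zero change is not an improvement under any cut-off, so the patient stays in the denominator as a non-responder. For SAQ, the inserted zeros pull mean changes towards zero and are analysed as if they had been observed.

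The sample size section describes a different analysis, in which the dropouts are absent and the remaining 102 patients respond at 85/70/50%. Two things are at stake. First, the only three-group power figure in the protocol does not apply to the FAS. Second, if dropout differs between arms, the rule turns that difference into a difference in response rates. This can plausibly happen, since section {11b} lists adverse events, low adherence and forbidden drugs among the withdrawal criteria.

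**Working it through.** **Inputs.** Rates 85/70/50%, alpha 0.05, 2 df, N = 102 evaluable, 20% dropout, N = 128 split 64/32/32 (section {14}); day-28 score only (Primary outcome, Tables 3 and 4); LOCF and FAS ({20c}).

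**Formulas.** W² = Σ wᵢ(pᵢ − p̄)² / [p̄(1 − p̄)], where wᵢ are the arm weights and p̄ the weighted mean rate. Noncentrality λ = N·W². Power is the probability that a noncentral chi-square exceeds the central 5% critical value.

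**Step 1: the plan's own figure.** Equal weights: p̄ = 0.6833, W² = 0.020556/0.216389 = 0.09499, W = 0.3082. With N = 102, λ = 9.689 and power = 0.802. This reproduces the stated chi-square and beta. Inflation: 102/0.8 = 127.5, so 128. With the actual 2:1:1 weights, W = 0.3216 and power for 102 completers is 0.837.

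**Step 2: the rule in {20c}, with 20% missing in each arm.** Rates become 0.85 × 0.8 = 0.68, 0.70 × 0.8 = 0.56 and 0.50 × 0.8 = 0.40, with all 128 patients in the denominator.

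- 2:1:1 weights: p̄ = 0.58, W² = 0.0132/0.2436 = 0.05419, λ = 128 × 0.05419 = 6.94, power = 0.651. Simulation at 64/32/32 (200,000 runs) gives 0.663.
- Equal weights: W = 0.2304, power = 0.642.

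**Step 3: other missing rates, N = 128.**

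| Missing day-28 score | Power, 2:1:1 | Power, equal weights |
|---|---|---|
| 5% | 0.856 | 0.832 |
| 10% | 0.791 | 0.771 |
| 15% | 0.721 | 0.706 |
| 20% | 0.651 | 0.642 |

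**Step 4: NXT vs BYHW (1 df, 2:1).**

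- Completers: 85% vs 70%, W² = 0.005/0.16 = 0.03125, N = 77, λ = 2.41, power = 0.342.
- Under LOCF at 20% missing: 68% vs 56%, p̄ = 0.64, W² = 0.0032/0.2304 = 0.01389, N = 96, λ = 1.33, power = 0.211.
- The stated 0.8554 is obtained by putting the three-group W = 0.3082 into a 1-df test with N = 96. With the two-group W (0.1768) and N = 96, power is 0.410 even without dropout.

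**Step 5: unequal dropout.** These figures are assumptions, not from the protocol. Let completers respond at 70% in two arms.

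- Dropout 15% vs 20%: 59.5% vs 56.0%, a gap of 3.5 points.
- Dropout 15% vs 25%: 59.5% vs 52.5%, a gap of 7 points.
- Dropout 10% vs 30%: 63% vs 49%, a gap of 14 points.

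**The case against.** **The 65% is conditional.** A reader might infer that every planned dropout becomes a non-responder and that FAS power simply is 65%. The documents do not support that. Section {14} does not define its drop rate as the share without a day-28 score. Section {11c} removes poor compliers from the per-protocol set after 28 days of treatment, so some of the planned losses may have a score that LOCF never touches. Patients who are never dosed are outside the FAS. At 10% missing or less, the shortfall from 80% is negligible with 2:1:1 weights. This stands: 65% is the figure if the whole planned 20% is missing.

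**The 80% is not expressly claimed for the FAS.** A reader might call the stated power wrong. It is correct for what it describes, 102 evaluable patients, and could be read with the per-protocol set. What remains is that the FAS, one of the two committed analyses of the primary outcome, has no power statement that fits it.

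**The assumed rates may already count dropouts as failures.** Power at N = 128 would then be 0.89 (equal weights) to 0.91 (2:1:1). But the inflation from 102 to 128 makes sense only if the rates belong to evaluable patients.

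**Counting dropouts as failures is defensible.** For a binary endpoint this is right, and section {11d} already does so for deterioration. However, {20c} does not declare it as the rule, section {14} does not size for it, and it gives no reason to enter a zero SAQ change as data.

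**The pairwise power.** A reader might blame LOCF for the whole drop from 85.5% to 21%. Most of that gap comes from the reused three-group effect size.

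**Conclusion.** The point holds as a should-fix. The mechanism follows from the protocol's own schedule, withdrawal rule and missing-data rule, and does not depend on the dropout rate: a dosed patient without a day-28 score is counted as not improved, and the SAQ change is set to zero.

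The size does depend on assumptions. If 20% of each arm is dosed and lacks a day-28 score, and 85/70/50% are completer rates, three-group FAS power is about 65%. Like for like, the loss is from 84% to 65% with 2:1:1 weights, or from 80% to 64% with the document's equal weights. For NXT vs BYHW, the part due to this rule is a fall from about 34% to 21%; the rest of the distance from 85.5% is a separate error in section {14}.

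A reader might also infer that the rule will create a false effect as large as the planned 15-point NXT–BYHW difference. That would take something like 10% vs 30% dropout, which nothing in the protocol predicts; an assumed 15% vs 25% gives 7 points. Such a gap is bias only if the target is the effect that would be seen had nobody dropped out.

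**What to change.** (a) In section {14}, state FAS power across 5–20% missing under the rule actually used, next to the figure for 102 evaluable patients. This calls for no further enrolment.

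(b) In section {20c}, replace LOCF.

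- **Binary primary outcome:** either declare explicitly that a missing day-28 score counts as non-response, or use multiple imputation by arm with the baseline score. Report the other as a named sensitivity analysis. Site should not enter the imputation within arm: six sites in an arm of 32 leave about five patients per cell. With so few predictors, multiple imputation will add little to a completer analysis and rests on a missing-at-random assumption, which is why both versions should be shown.
- **SAQ change:** use multiple imputation, or a baseline-adjusted analysis of observed values, instead of inserting zero change.
- **Deterioration rule in {11d}:** keep it as written.

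The cost is a little more programming and a less favourable stated power, with no new visits. The Trial status section reports that recruitment is under way and no analysis has been done, so the change can still be made before any results are seen.
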